#### Study sites.

The list of study sites is available on https://clinicaltrials.gov/ct2/show/NCT03418844 .

### Assessments

**Step 1**

All participants are asked to complete several validated self-reported questionnaires including standardized and validated questionnaires (Table 2):
**Fatigue Questionnaire (Multidimensional Fatigue Inventory: MFI-20)**: includes 20 items measuring 5 dimensions of fatigue (general and physical perception of fatigue, reductions in motivation and activity, and mental fatigue) [29, 30].**Modified Living Conditions Questionnaire**: with objective questions on fertility monitoring and parental plans, social reintegration, career path and professional situation, care consumption and patient expectations regarding post-cancer management. This questionnaire used in previous surveys [28–31].**Functional assessment of cancer therapy scale general** (FACT-G) and module for **ovarian cancer** (FACT-O): symptomatic scale comprising 12 items assessing abdominal symptoms, other adverse effects of chemotherapy, hormonal disorders, body image, sexuality and attitude towards the disease and its treatments [32].**Hospital Anxiety and Depression Scale** (HADS): A 14-item structured self-administered questionnaire to screen for anxiety and depression. This scale has been validated in oncology [33].**Peripheral Neurotoxicity Questionnaire** (FACT/GOG-NTX): specific scale composed of 11 items probing the following points: numbness or tingling, discomfort, arthralgia, cramps, general weakness, tinnitus, hearing problems, problems buttoning clothes, deep sensitivity problems (touching small objects), walking problems.**FACT-Cog Questionnaire**: A self-questionnaire that subjectively assesses patients’ cognitive complaints. Patients are asked to rate their feelings on a scale ranging from 0 “not at all” to 4 “very much”. The 37 items cover 4 dimensions: perception of cognitive impairment, impact on QoL, comments from third parties, perception of cognitive abilities [34].**Insomnia Severity Index (ISI)**: consists of 7 items used to quantitatively assess how much the person is affected by insomnia [35].**Physical Activity Questionnaire** (IPAQ): has the advantage of providing a measure of overall physical activity as well as its frequency and intensity.**Self-administered Euroqol Questionnaire** (EQ-5D 5 L): allows the evaluation of a utility score associated with a health condition. The value set based on societal preferences of the French population recently published will be used [36].

**Table 2 Tab2:** Self-reported questionnaires used in study

Questionnaires	Scoring	Definition of scoring

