**Methods:**

Using self-reported questionnaires, chronic fatigue and quality of life are compared between 134 ovarian cancer survivors (cancer-free ≥2 years after treatment) treated with surgery and chemotherapy and 2 control groups (67 ovarian cancer survivors treated with surgery alone and 67 age-matched healthy women). Medical data are collected from patient records. In the second step evaluating the long-term side-effects of chemotherapy, a subgroup of 90 patients treated with chemotherapy and 45 controls undergo the following work-up: cardiovascular evaluation (clinical examination, non-invasive cardiovascular tests to explore heart disease, blood tests), pulmonary function testing, audiogram, metabolic and hormonal blood tests. Costs of sequelae will be also assessed. Patients are selected from the registry of the INCa French Network for Rare Malignant Ovarian Tumors, and healthy women by the ‘Seintinelles’ connected network (collaborative research platform).

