**Assessment and comparison of the costs of sequelae in the 2 groups of patients**		
Euroqol (EQ-5D 5 L) questionnaire	Generic measure for clinical and economic assessment	Utility score associated with state of health.

^a^: Clinically significant difference: variation of 5%, ^b^: Responses are categorized into three levels of physical activity: low (<moderate); moderate (3 or more days/week of vigorous activity of at least 20 min/day or 5 or more days/week of moderate activity, or 30 min/day walking) and high (vigorous activity on at least 3 days or 7 days/week of any combination of walking, moderate or vigorous intensity activities). *MFI* Multidimensional Fatigue Inventory -*QoL* Quality of Life, *FACT-G* General Functional Assessment of Cancer Therapy, *PWB* Physical Well-Being, *SWB* Social/family Well-Being, *EWB* Emotional Well-Being, *FWB* Functional Well-Being, *EOC* Epithelial Ovarian Cancer, *FACT-O* Functional Assessment of Chronic Therapy- Ovarian subscale, *FACT-F* Functional Assessment of Chronic Therapy-Fatigue subscale, *FACT/GOG-Ntx* Functional Assessment of Cancer Therapy/ Gynecologic Oncology Group–Neurotoxicity subscale, *FACT-Cog* Functional Assessment of Cancer Therapy-Cognitive, *TOI* Trial Outcome Index, *ISI* Insomnia Severity Index, *HADS* Hospital Anxiety and Depression Scale, *IPAQ* International Physical Activity Questionnaire, *NA* Not Adapted

Volunteers from both patient groups receive information sheets and the different questionnaires from their oncologists during the follow-up consultation or by mail. They are asked to return completed questionnaires anonymously in a stamped preaddressed envelope. A reminder is sent if necessary.

**Patient’s medical data** (date and context of disease diagnosis, treatment modalities, fertility-sparing, second cancer, and comorbidities (focus on cardiovascular diseases, pulmonary and metabolic disorders)) are collected from patient records. For the healthy control group, the website administrator of the Seintinelles network publishes the study information and the questionnaires on their website, and contacts registered healthy women to complete the different questionnaires online.

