**Step 2**

The study (objectives and constraints) is proposed to both patient groups (90 patients with surgery and BEP chemotherapy and 45 with surgery alone) by GINECO oncologists. Once signed informed consent has been obtained, patients undergo cardiovascular, respiratory, hearing, metabolic and hormonal work-up. The planned tests are detailed in Table 3.

**Table 3 Tab3:** Overview of study assessments of the VIVROVAIRE TR Study

	Study Period		
	Enrollment	Step 1	Step 2
**Eligibility Screen**	**•**		
**Informed Consent**	**•**		
**Disease medical history**	**•**		
**Chronic fatigue, quality of life and late effects of chemotherapy**		**•**	
✓ Fatigue (MFI-20^a^)		**•**	
✓ Quality of life (FACT-G^b^/FACT-O^c^)		**•**	
✓ Neurotoxicity (FACT/GOG-NTX^d^)		**•**	
✓ Cognition (FACT-Cog^e^)		**•**	
✓ Day-to-day life (Living condition questionnaire)		**•**	
✓ Anxiety /Depression (HADS^f^)		**•**	
✓ Insomnia (ISI^g^)		**•**	
✓ Physical activity (IPAQ^h^)		**•**	
✓ EQ-5D^i^ (For patients only)		**•**	
**Specialized medical examination**			**•**

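### FACT-O goes to healthy women although part of it concerns disease and treatment, so the healthy-control contrast on FACT-O and FACT-O/TOI is partly built in; the text and Table 3 also disagree on EQ-5D-5L

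*Protocol article*

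**What the plan says.** The Abstract (Methods) sets the comparison: "chronic fatigue and quality of life are compared between 134 ovarian cancer survivors" and two control groups, one treated with surgery alone and one of age-matched healthy women.

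The Assessments section, Step 1, opens with "All participants are asked to complete several validated self-reported questionnaires". The list that follows contains both FACT-O and EQ-5D-5L and names no exception. FACT-O is introduced as a 12-item symptom scale "assessing abdominal symptoms, other adverse effects of chemotherapy, hormonal disorders, body image, sexuality and attitude towards the disease and its treatments".

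Table 3 schedules "Quality of life (FACT-G^b^/FACT-O^c" in Step 1 without any group restriction. A few rows further down it does apply one: "EQ-5D^i^ (For patients only".

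The text after Table 2 says that the administrator of the volunteer network "contacts registered healthy women to complete the different questionnaires online". It mentions no subset of questionnaires and no adapted version.

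Table 2 places EQ-5D-5L under the heading "Assessment and comparison of the costs of sequelae in the 2 groups of patients".

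**The concern.** Two of the content areas listed for FACT-O presuppose a history that healthy women do not have: effects of chemotherapy, and how the respondent regards her illness and its treatment. Healthy controls are by definition women without cancer (Table 1).

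Such a woman can leave these items blank, which puts missing items in one group only. She can also answer that there is no effect. Table 2 says that a lower FACT-O score means more severe symptoms, so for the chemotherapy-effect items that answer moves her score towards the better end. For the attitude items even the direction is unknown, because their wording is not given.

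Either way, part of the difference between survivors and healthy women would record who had cancer and treatment, yet it could be reported as a loss of quality of life.

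The EQ-5D-5L conflict is a separate matter. The Step 1 text gives it to everyone and Table 3 gives it to patients only. Sites and the volunteer platform cannot follow both.

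**Working it through.** **1. Who completes what.** Table 3 lists nine Step 1 instruments: MFI-20, FACT-G with FACT-O (one row), FACT/GOG-Ntx, FACT-Cog, the living conditions questionnaire, HADS, ISI, IPAQ and EQ-5D. Eight rows carry no restriction and one (EQ-5D) is marked for patients. The table therefore marks a patient-only instrument where one is meant, and FACT-O is not marked. This agrees with the Step 1 lead-in sentence and with the text on the volunteer platform.

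**2. Where FACT-O enters.** Table 2 defines TOI as PWB + FWB + the concerns subscale. With the tabulated ranges, 28 + 28 + 44 = 100, which reproduces the stated 0–100 range for FACT-O/TOI. FACT-O thus supplies 44 of 100 TOI points, and any built-in difference in FACT-O passes into the TOI unchanged.

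**3. Where it does not enter.** The FACT-G total is 28 + 28 + 24 + 28 = 108, as Table 2 states, and contains no FACT-O item. MFI-20, HADS, ISI and IPAQ are separate instruments, and the article describes none of them as specific to cancer or its treatment. The Step 1 sample size is built on fatigue by MFI-20 and does not depend on this point.

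**4. Can the size be computed?** No. It would need the number of items that refer to disease or treatment, how healthy women answer them, and how survivors answer them. The article gives none of these. Even the number of scored items is unclear: 12 items scored 0–4 would span 12 × 4 = 48, whereas the tabulated 44 corresponds to 11 × 4.

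The only yardstick is the Table 2 footnote that treats a 5% variation as clinically significant. It does not say 5% of what. Read as 5% of the range (an assumption), it is 0.05 × 44 = 2.2 points for FACT-O and 0.05 × 100 = 5 points for FACT-O/TOI. With a threshold of 2.2 points, a one-category difference on three items (3 × 1 = 3 points) would pass it. This shows that the scale is sensitive to a few items. It does not estimate the bias.

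**5. EQ-5D-5L, side by side.** Step 1 text: on the list for all participants. Table 3: patients only. Table 2: placed under the cost comparison of the two patient groups. The last two agree with each other and conflict with the first.

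**The case against.** **The article condenses a longer protocol.** An adapted form for healthy women may be specified there, and Table 3 has no group columns, so a missing restriction is weak evidence. This stands in part. However, the point does not rest on silence: the article states that all participants complete the list, and restricts a different instrument explicitly.

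**The items may be plain symptom questions.** If so, a healthy woman who reports no symptom gives a true answer. This stands for abdominal symptoms, hormonal symptoms, body image and sexuality, which any woman can report on. It may stand for some items described as chemotherapy effects. It cannot stand for content on attitude to an illness and treatment that she never had.

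**Surgery-alone patients had no chemotherapy either.** True, but they have had the disease and a treatment, so the attitude content applies to them. A difference from them in chemotherapy effects is what the study sets out to measure.

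**Keeping EQ-5D for patients looks deliberate.** Table 2 ties it to the cost comparison between the patient groups, and no objective asks for a utility comparison with healthy women. This stands. Extending it is a preference; only the contradiction in the text is an error.

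**Conclusion.** The point holds in a narrow form. As the article is written, the survivor versus healthy-women contrasts on the FACT-O score and on FACT-O/TOI mix real differences with differences that follow from group membership or from one-sided missing items. This rests on the article's own description of the content and on the assumption that healthy women receive the module unadapted. The size is not computable.

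A reader might infer more in three ways, none of which the document supports:

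- **That the whole quality-of-life comparison with healthy women fails.** HADS, ISI, IPAQ and the separately scored FACT-G are also given to them and are not affected by this point, nor is the primary fatigue endpoint. How well FACT-G itself suits healthy women cannot be judged, since its items are not shown.
- **That EQ-5D-5L is the only measure healthy women could answer.** Table 3 leaves MFI-20, HADS, ISI and IPAQ open to them.
- **That the built-in difference is 8–16 of 44 points.** That figure assumes two to four affected items, each with survivors at the worst category and healthy women at the best (2 × 4 = 8, 4 × 4 = 16). It is a ceiling under an assumed item count, not an estimate.

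Severity is minor: only secondary endpoints are concerned. The EQ-5D-5L contradiction is a plain inconsistency.

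**What to change.** 1. Report the FACT-O total and FACT-O/TOI only for chemotherapy versus surgery alone, and say so in the Planned analysis section and in Table 2.
2. Keep on the healthy women's online form the FACT-O items that do not refer to disease or treatment, such as those on abdominal symptoms, hormonal symptoms, body image and sexuality. List them, and limit any healthy-control contrast on FACT-O to them. Dropping the module from healthy women altogether would be worse, because FACT-O is the only listed scale described as covering sexuality, body image and hormonal disorders, which bear on the secondary objectives.
3. Reconcile the Step 1 text with Table 3 on who completes EQ-5D-5L. Extending it to healthy women is optional. The study is recruiting, so if the healthy women's form has so far omitted it, those who have already answered would lack it.

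The cost is a few lines of text, a short item list and table footnotes. No collected data are lost, and PWB and FWB remain available through FACT-G. The downside is that there would be no FACT-O total or FACT-O/TOI for healthy women.

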**Chronic fatigue**		
**Fatigue** MFI-20 items	5 dimensions of fatigue: -General fatigue -Physical fatigue -Reduced motivation -Reduced activity -Mental fatigue	High score indicates high level of fatigue
**Global quality of life**^**a**^		
**Global QoL** FACT-G	4 dimensions: 0–4 Likert scale - PWB: 7 items, score range: 0–28 - SWB: 7 items, score range: 0–28 - EWB: 6 items, score range: 0–24 - FWB: 7 items, score range: 0–28 Total score: 0–108	A lower score indicates a lower QoL dimension
**Additional concerns subscale**^**a**^		
**EOC specific concerns** FACT-O	0–4 Likert scale Score: 0–44	A lower score indicates a severe symptom
		A lower score indicates a high level of fatigue
**Neurotoxicity** FACT/GOG-Ntx	0–4 Likert scale Score range: 0–44	A lower score indicates a worse neuropathy Score < 33 ≈ Severe neuropathy
**TOI = PWB + FWB + concerns subscale**^**a**^		
FACT-F/TOI	Score range: 0–108	A lower score indicates a severe symptom
FACT/GOG-Ntx/TOI	Score range: 0–100	
FACT-Cog	Score range: 0–100	
FACT-O/ TOI	Score range: 0–100	
**Other dimensions of QoL**		
**Anxiety & Depression** HADS	Anxiety: 7 items, score range: 0–21 Depression:7 items, score range: 0–21	Score ≥ 8 ≈ elevated anxiety, Score ≥ 8 ≈ elevated depression,
**Sleep disturbance** ISI	0–5 Likert scale Score range: 0–28	A higher total score indicates more severe sleep difficulties Score 22–28 ≈ Severe clinical insomnia
**Physical activity** IPAQ	3 levels of physical activity (categorical score)^b^	High/ moderate/low level of physical activity
**Conditions of life**		
**Living conditions** questionnaire [25]	Daily life of participants (family, social and professional situation)	NA
**Assessment and comparison of the costs of sequelae in the 2 groups of patients**		
Euroqol (EQ-5D 5 L) questionnaire	Generic measure for clinical and economic assessment	Utility score associated with state of health.

^a^: Clinically significant difference: variation of 5%, ^b^: Responses are categorized into three levels of physical activity: low (<moderate); moderate (3 or more days/week of vigorous activity of at least 20 min/day or 5 or more days/week of moderate activity, or 30 min/day walking) and high (vigorous activity on at least 3 days or 7 days/week of any combination of walking, moderate or vigorous intensity activities). *MFI* Multidimensional Fatigue Inventory -*QoL* Quality of Life, *FACT-G* General Functional Assessment of Cancer Therapy, *PWB* Physical Well-Being, *SWB* Social/family Well-Being, *EWB* Emotional Well-Being, *FWB* Functional Well-Being, *EOC* Epithelial Ovarian Cancer, *FACT-O* Functional Assessment of Chronic Therapy- Ovarian subscale, *FACT-F* Functional Assessment of Chronic Therapy-Fatigue subscale, *FACT/GOG-Ntx* Functional Assessment of Cancer Therapy/ Gynecologic Oncology Group–Neurotoxicity subscale, *FACT-Cog* Functional Assessment of Cancer Therapy-Cognitive, *TOI* Trial Outcome Index, *ISI* Insomnia Severity Index, *HADS* Hospital Anxiety and Depression Scale, *IPAQ* International Physical Activity Questionnaire, *NA* Not Adapted

Volunteers from both patient groups receive information sheets and the different questionnaires from their oncologists during the follow-up consultation or by mail. They are asked to return completed questionnaires anonymously in a stamped preaddressed envelope. A reminder is sent if necessary.

**Patient’s medical data** (date and context of disease diagnosis, treatment modalities, fertility-sparing, second cancer, and comorbidities (focus on cardiovascular diseases, pulmonary and metabolic disorders)) are collected from patient records. For the healthy control group, the website administrator of the Seintinelles network publishes the study information and the questionnaires on their website, and contacts registered healthy women to complete the different questionnaires online.
**Step 2**

The study (objectives and constraints) is proposed to both patient groups (90 patients with surgery and BEP chemotherapy and 45 with surgery alone) by GINECO oncologists. Once signed informed consent has been obtained, patients undergo cardiovascular, respiratory, hearing, metabolic and hormonal work-up. The planned tests are detailed in Table 3.

**Table 3 Tab3:** Overview of study assessments of the VIVROVAIRE TR Study

	Study Period		
	Enrollment	Step 1	Step 2
**Eligibility Screen**	**•**		
**Informed Consent**	**•**		
**Disease medical history**	**•**		
**Chronic fatigue, quality of life and late effects of chemotherapy**		**•**	
✓ Fatigue (MFI-20^a^)		**•**	
✓ Quality of life (FACT-G^b^/FACT-O^c^)		**•**	
✓ Neurotoxicity (FACT/GOG-NTX^d^)		**•**	
✓ Cognition (FACT-Cog^e^)		**•**	
✓ Day-to-day life (Living condition questionnaire)		**•**	
✓ Anxiety /Depression (HADS^f^)		**•**	
✓ Insomnia (ISI^g^)		**•**	
✓ Physical activity (IPAQ^h^)		**•**	
✓ EQ-5D^i^ (For patients only)		**•**	
**Specialized medical examination**			**•**
**Cardiovascular:**			
a) Cardio-vascular medical examination with non-invasive tests to explore heart disease (by a cardiologist)			**•**
- Electrocardiogram			**•**
- Echocardiography			**•**
-Coronary endothelium-dependent vasoreactivity testing (optional exam)			**•**
b) Non-invasive vascular tests to explore atherosclerosis:			**•**
- Systolic index of lower and upper limbs,			**•**
-Ultrasound images to measure carotid intima media thickness			**•**
- Capillaroscopy to assess Raynaud’s syndrome (optional exam)			**•**
c) Specific cardiac biological tests:			**•**
High-sensitive cardiac troponin, BNP, Von Willebrand factor (VWf), tissular Plasminogen Activator (t-PA).			**•**
**Respiratory & Hearing:**			**•**
- Respiratory Function Tests (RFT)			**•**
- Audiogram			**•**
**Blood sampling: exploring metabolic and hormonal disorders**			**•**
- Hormonal assessment: sex hormone binding globulin (SHBG), Luteinizing hormone (LH), Follicle-stimulating hormone (FSH), Estradiol, Anti-Müllerian hormone (AMH), thyroid stimulating hormone (TSH).			**•**
-Carbohydrate-lipid balance: fasting blood glucose and insulin, lipid fractions, triglycerides;			**•**
- Osteocalcin blood Tests: calcium, phosphorus, vitamin D			**•**
- Renal assessment: ionograms, creatinine level			**•**
-Hepatic assessment: transaminases (TGO, TGP), Aspartate Aminotransferase (ASAT), Alanine Aminotransferase (ALAT), Alkaline Phosphatase (PAL), Gamma-glutamyl transferase (GGT), Lactate dehydrogenase (LDH			**•**
- C-Reactive Protein Test ultrasensitive			**•**

^a^*MFI* Multidimensional Fatigue Inventory;^b^*FACT-G* General Functional Assessment of Cancer Therapy; ^c^*FACT-O* Functional Assessment of Chronic Therapy- Ovarian subscale,^d^*FACT/GOG-Ntx* Functional Assessment of Cancer Therapy/ Gynecologic Oncology Group–Neurotoxicity subscale; ^e^*FACT-Cog* Functional Assessment of Cancer Therapy-Cognitive;^f^*HADS* Hospital Anxiety and Depression Scale,^g^*ISI* Insomnia Severity Index,^h^*IPAQ* International Physical Activity Questionnaire; ^i^EQ-5D Euroqol questionnaire

Patients who have agreed to participate in the second stage will undergo the following medical check-up:

**Cardiac check-up** which will include:
A cardiac consultation including the measurement of systolic pressure index;An electrocardiogram;Carotid Doppler ultrasound with measurement of carotid intima media thickness and arterial; vasoreactivity (arterial elasticity, carotid pulse wave velocity) (optional for vasoreactivity),A capillaroscopy: search for Raynaud’s syndrome (optional);A humeral Doppler ultrasound for study of flow-mediated humeral vasodilatation (optional);A trans-thoracic echocardiography 2D, 2D Strain (optional) and ± 3D;A blood test comprising an enzyme profile: ultra-sensitive troponin, BNP, von Willebrand factor assay, and t-PA.

### Lung and hearing examination

Respiratory Function Tests (RFT);Tonal audiogram.

**Blood sampling**: exploring metabolic and hormonal disorders.
Carbohydrate-lipid balance: fasting blood glucose and insulin, lipid fractions, triglycerides;Hepatic: transaminases (TGO, TGP), Aspartate Aminotransferase (ASAT), Alanine Aminotransferase (ALAT), Alkaline Phosphatase (PAL), Gamma-glutamyl transferase (GGT), Lactate dehydrogenase (LDH);Hormone balance: sex hormone binding globulin (SHBG), Luteinizing hormone (LH), Follicle-stimulating hormone (FSH), Estradiol, Anti-Müllerian hormone (AMH), thyroid stimulating hormone (TSH).Osteocalcic balance: calcium, phosphorus, vitamin D;Renal assessment: ionogram, creatinine;C-reactive protein (CRP) + highly sensitive CRP.

Compensation is offered to cover the costs of transport and to compensate one day off work.

The overview of study assessments and procedures can be found in Table 3.

**The costs of the sequelae** will be estimated for the 140 patients. Standard unit costs will be calculated for each type of sequelae using data from the financial departments of the participating hospitals, as well as the published literature [37]. The average costs will be assessed and compare between both patient groups. One-way sensitivity analyses will be conducted by varying parameters by plus or minus 20% and illustrated graphically in a Tornado diagram.

